**Key secondary endpoints**	
1.	Change from baseline to *months 12 and 24* in *peripheral enthesitis*, as assessed by WB-MRI, in patients with axSpA and PsA treated with ixekizumab.
2.	Change from baseline to *months 12 and 24* in *peripheral joint inflammation*, as assessed by WB-MRI, in patients with axSpA and PsA treated with ixekizumab.
3.	Change from baseline to *month 24* in *total inflammatory burden in the entire body* (peripheral and axial joints and entheses), as assessed by WB-MRI, in patients with axSpA and PsA treated with ixekizumab.
4.	Description of *patterns of structural damage in sacroiliac joints and spine* in patients with axSpA and PsA by conventional MRI methods, MRI-based synthetic CT, low-dose CT, and radiography.
5.	Description of *changes in structural damage in sacroiliac joints and spine* in patients with axSpA and PsA by conventional MRI methods, MRI-based synthetic CT, low-dose CT, and radiography, during 2 years of therapy with ixekizumab.
**Other secondary endpoints**	
1.	Change from baseline to *months 4, 12, and 24* in *axial inflammation*, as assessed by MRI, in patients with axSpA and PsA treated with ixekizumab, including separately in the posterolateral elements of the spine (facet joints, costovertebral joints, transverse processes, spinous processes, and perientheseal soft tissues) and in the vertebral bodies.
2.	Change from baseline to *months 4 and 24* in *peripheral enthesitis*, as assessed by WB-MRI, in patients with axSpA and PsA treated with ixekizumab.
3.	Change from baseline to *months 4 and 24* in *peripheral joint inflammation*, as assessed by WB-MRI, in patients with axSpA and PsA treated with ixekizumab.
4.	Change from baseline to *month 4* in *total inflammatory burden in the entire body* (peripheral and axial joints and entheses), as assessed by WB-MRI, in patients with axSpA and PsA treated with ixekizumab.
5.	*Description of differences between axSpA and PsA* inflammatory disease manifestations and their response to ixekizumab therapy at months 4, 12, and 24 (by sacroiliac joint and spine MRI and by WB-MRI).
6.	*Development of improved MRI and CT assessment methods* for axial structural damage assessment.
7.	Description of the *relationship between clinical, patient-reported, and imaging findings* at baseline and during ixekizumab therapy.

*WB-MRI* Whole body magnetic resonance imaging, *axSpA* axial spondyloarthritis, *PsA* Psoriatic arthritis, *CT* computed tomography

### Statistics

#### Sample size calculation

The primary hypothesis of this study is that ixekizumab will reduce the total inflammatory burden in the entire body of patients with axSpA and PsA, as assessed by WB-MRI. All patients in this study will be treated with ixekizumab and the primary endpoint relates to identifying changes within groups. A guiding sample size calculation was done.

A previous investigator-initiated study with 53 axSpA patients treated with a bDMARD (golimumab) using WB-MRI as an outcome measure showed that the mean change in MRI-total inflammation (MRI axial inflammation + MRI peripheral inflammation (joints and entheses)) at week 52 was 24.8 (*p* < 0.001) with a standard error of 3.6 [55].

The change in WB-MRI total inflammation is the primary endpoint in the current study. If the expected mean of the paired differences is 24.8 and the expected standard deviation is 26.2 (corresponding to a standard error of 3.6) the study would require a sample size of 12 (numbers of pairs) to achieve a power of 0.80 and a level of significance of 0.05 (two-sided).

With an expected drop-out rate of 20% at month 12 the required sample size would be 14 patients.

It is planned to include 65 patients (≥25 with each diagnosis).

Sub-group analyses in regard to the primary endpoints for all groups (axSpA vs. PsA, WB-MRI remission vs. WB-MRI non-remission and clinical responders vs. clinical non-responders) are planned. For this matter, the calculated sample size is considered appropriate to detect a statistically significant change in the total inflammatory burden in the entire body as assessed by WB-MRI at month 12 in both the overall study population and in the individual sub-groups during treatment with ixekizumab.

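### The sample size statement claims adequacy in every sub-group, but the one calculation behind it does not support that claim for the remission and clinical-response strata

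*Protocol article*

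**What the plan says.** All of the following is in the protocol article.

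- **Source of the inputs (Sample size calculation).** "A previous investigator-initiated study with 53 axSpA patients treated with a bDMARD (golimumab") supplies the effect. Its mean change in total inflammation at week 52 was 24.8, with a standard error of 3.6.
- **Calculation (same section).** "If the expected mean of the paired differences is 24.8 and the expected standard deviation is 26.2". From these values the section arrives at 12 pairs for 80% power at a two-sided 5% level. It calls this calculation guiding.
- **Drop-out (same section).** "With an expected drop-out rate of 20% at month 12 the required sample size would be 14 patients".
- **Enrolment (same section).** "It is planned to include 65 patients (≥25 with each diagnosis").
- **Adequacy claim (same section).** Sub-group analyses of the primary endpoint are planned by diagnosis, by WB-MRI remission and by clinical response. The section then says that "the calculated sample size is considered appropriate to detect a statistically significant change in the total inflammatory burden", and applies this to the overall population and to the individual sub-groups, during ixekizumab treatment.
- **How the strata are formed (Statistical analysis).** Clinical responders are those with ASDAS or DAPSA low disease activity at months 4, 12 and 24. Remission status comes from the sum of WIPE, CANDEN spine and SPARCC SIJ, which is also the primary endpoint score.
- **What happens to non-responders (Assessments).** At a major visit they change treatment and remain in follow-up.

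No effect, SD or expected size is given for any sub-group. Only the diagnosis groups have a minimum size.

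**The concern.** A calculation for one group with one effect size is used to vouch for six sub-groups. It extends to them only if each is large enough and changes by about as much as the average axSpA patient in the source study. The protocol never states that second condition, but 24.8 is the only effect it supplies.

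The condition is hard to accept for non-remitters, who are identified on the score whose change is being tested. It is open to doubt for clinical non-responders, who are identified by their disease activity after treatment starts. Either stratum could also be small, since neither its size nor its expected share is fixed.

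What is at stake is how a null result would be read. If non-responders or non-remitters show no significant change, the printed statement invites the conclusion that an adequately sized analysis found none. The design may not be able to support that conclusion.

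There is also a wording conflict. The claim refers to change during ixekizumab treatment, but a patient classed as a non-responder at month 4 changes treatment, so that patient's month-12 change may not be on ixekizumab.

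**Working it through.** **Inputs from the document.** Mean paired change 24.8; standard error 3.6 with n = 53; two-sided alpha 0.05; power 0.80; drop-out 20%; 65 patients, at least 25 per diagnosis.

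**Assumed, because the document gives none.** Stratum sizes of 10, 20 and 26 evaluable patients; a stratum effect of 100% or 50% of 24.8; SD 26.2 within strata unless stated otherwise.

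**1. Reproduce the plan's figure.**
- SD = 3.6 × √53 = 26.2.
- Standardised change d = 24.8 / 26.2 = 0.947.
- Power of the paired t-test uses the noncentral t distribution with n − 1 degrees of freedom and noncentrality d√n.
- n = 10 gives 75.9%, n = 11 gives 80.7%, n = 12 gives 84.7%.

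The exact minimum is 11. The stated 12 is close and slightly conservative.

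**2. Drop-out step.** 12 / 0.8 = 15, whereas 14 × 0.8 = 11.2, which is below 12. The stated 14 is what the exact minimum of 11 would give (11 / 0.8 = 13.75, rounded up).

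**3. Where the claim holds.**
- Overall: 65 × 0.8 = 52 evaluable. Power is above 99% at 24.8 and 92% at half of it.
- Each diagnosis group: 25 × 0.8 = 20 evaluable. Power is 98% at 24.8 and stays at 80% down to a change of 17.3 (17.3 / 24.8 = 70%).

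**4. Where it is unsupported.** Half the effect is 12.4, so d = 12.4 / 26.2 = 0.473.

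| Evaluable in stratum | Power at 24.8 | Power at 12.4 |
|---|---|---|
| 10 | 76% | 27% |
| 20 | 98% | 52% |
| 26 | >99% | 64% |
| Needed for 80% | 11 | 38 |

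**5. Sensitivity to the SD.** If two equal strata change by 12.4 and 37.2 (average 24.8) and the total SD is 26.2, each stratum mean lies 12.4 from the overall mean. The within-stratum SD is then √(26.2² − 12.4²) = √(686.4 − 153.8) = 23.1. With d = 12.4 / 23.1 = 0.537, power at 26 is about 75% and 30 pairs are needed. The shortfall shrinks but remains.

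**6. Precision that the design does give.** The 95% half-width is t × 26.2 / √n.
- n = 52: 2.008 × 26.2 / √52 = 7.3 points.
- n = 20: 2.093 × 26.2 / √20 = 12.3 points.

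**The case against.** The strongest reply is that the calculation is labelled guiding, that 65 is far more than 14, that the affected analyses are stratifications of a well-powered primary analysis, and that a detailed SAP will precede any analysis. The first three are true and limit the weight of the point. They do not rescue the sentence, which states adequacy in the sub-groups without qualification, and a later SAP cannot supply support that the printed claim lacks.

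It can also be said that the halved effect is the reviewer's assumption, and that clinical non-response is judged by ASDAS or DAPSA and may track MRI change poorly. That stands: a halved change in clinical non-responders is not established. The opposite is not established either, and the claim needs it. For non-remission the link to the endpoint score is built in.

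Three stronger readings are tempting, and the document does not support them.

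- **That the claim also fails for PsA.** No PsA or ixekizumab figure is given. But at least 25 patients per diagnosis are planned, and on the only inputs supplied 20 evaluable give 98%. Carrying axSpA figures over to PsA is an extrapolation, as is carrying golimumab over to ixekizumab for axSpA. The remedy for both is to state the assumption.
- **That the study claims power to compare axSpA with PsA.** The section refers to changes within groups, and Table 3 calls the difference between diagnoses a description. Low power for such a comparison therefore refutes nothing that is stated.
- **That the slip from 15 to 14 undermines the sample size.** It is one patient, with 65 planned.

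**Conclusion.** The point holds in a limited form and is a moderate correction of wording. The calculation is sound for the whole population and, if the golimumab axSpA effect and SD carry over, for each diagnosis group. It does not support the adequacy claim for the remission and clinical-response strata, because it needs about 11 evaluable patients and the full 24.8-point change in each, and the protocol secures neither.

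How large the shortfall is depends on assumed stratum sizes, effects and SD, so the percentages for those strata are illustrations and not predictions. The conclusion that the claim is unsupported does not depend on any one of them.

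**What to change.** Rewrite the last paragraph of Sample size calculation.

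- Limit the adequacy statement to the overall population and to the two diagnosis groups. For the latter, state the assumption that the golimumab axSpA effect and SD apply to ixekizumab and to PsA.
- Declare the remission and clinical-response strata exploratory and report them with 95% confidence intervals. Give the available precision: about 7.3 points either side with 52 evaluable and 12.3 with 20.
- Say that the calculation does not cover the between-group comparisons listed under Statistical analysis.
- Reconcile the reference to change during ixekizumab treatment with Assessments, where non-responders change treatment and stay in follow-up.
- Correct 14 to 15, or state that 14 follows from the exact minimum of 11 pairs.

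The cost is one paragraph and a less favourable statement of what the sub-group analyses can show. Enrolment does not change.

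Suggested wording: *The sample size is adequate for month-12 change in the overall population and, assuming that the effect and SD seen with golimumab in axSpA apply, in each diagnosis group. Analyses by WB-MRI remission and clinical response are exploratory and will be reported with 95% confidence intervals. Comparisons between groups were not powered.*

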### Statistical analysis

The primary analysis will be the intention-to-treat (ITT) population, which comprises all included patients. An additional Per Protocol (PP) analysis will be done as a robustness analysis. The entire patient population will be analyzed for the primary and secondary endpoints. Furthermore, patients will be stratified based on their diagnosis and WB-MRI remission status (remission versus non-remission). Additionally, patients will be stratified as clinical responders versus non-responders at months 4, 12, and 24, based on the presence/absence of ASDAS low disease activity (≤2.1) for patients with axSpA and DAPSA low disease activity (≤14) for patients with PsA. The total inflammatory burden in the entire body, including both peripheral and axial joints and entheses will be assessed at multiple time points - month 0 (baseline), month 4, month 12 (the primary endpoint), and month 24. The total inflammatory burden in the entire body and the WB-MRI remission status will be determined using the sum score of WB-MRI scoring methods for peripheral (WIPE) and axial (CANDEN spine and SPARCC SIJ) inflammation. Further, patients (both the entire patient population and sub-groups stratified by diagnosis, WB-MRI remission and clinical responsiveness) will be evaluated separately for peripheral enthesitis and joint inflammation (using WIPE), and axial inflammation (using CANDEN spine and SPARCC SIJ).

The statistical analyses will include descriptive statistics for all patients (number, median/mean/range of conventional and experimental data), comparisons between groups and within groups (axSpA vs. PsA, WB-MRI remission vs. WB-MRI non-remission, and clinical responders vs. clinical non-responders).

Changes within all patients and the described sub-groups are planned to be analyzed with paired T-test (in case of normal distribution), and Wilcoxon signed rank test (in case of non-normal distribution). Comparisons between the sub-groups will be analyzed with an unpaired T-test (in case of normal distribution) or Mann-Whitney U test (non-normal distribution). Furthermore, AUC (area under the curve) values for biomarkers as well as clinical and imaging parameters will be calculated in addition to correlation analysis comparing imaging and clinical findings (in case of normal distribution) or Spearman’s test of rank correlation (non-normal distribution). Finally, standardized response mean (SRM) will be used to assess responsiveness, and an analysis of predictors will be performed by doing univariate followed by multivariable linear and logistic regression analysis. A detailed statistical analysis plan (SAP) will be made before the start of any analyses.

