### Assessments

During the 2-year study period, patients will have eight visits to the outpatient clinic, three of which are major assessment visits (months 4, 12, and 24) (see Fig. 1, dark blue arrows). At the major assessment visits, treatment efficacy, and disease activity are evaluated. Patients with ASDAS low disease activity (ASDAS ≤2.1) (axSpA) or DAPSA low disease activity (DAPSA ≤14) (PsA) continue treatment with sc. inj. ixekizumab 80 mg every 4 weeks. Patients, who are not responding (defined as having ASDAS > 2.1 or DAPSA > 14), change treatment at the discretion of the treating rheumatologist and according to the available guidelines from the Medicine Council, Danish Regions (Medicinrådet, Danske Regioner), and they continue to be followed in the study.

All protocol-related assessments will be entered into an electronic case report dedicated to the DAPHNE study.

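### The month-12 and month-24 clinical responder strata ignore which drug the patient is on, so patients who improved after a change of treatment are grouped with those who responded to ixekizumab.

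*Protocol article*

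**What the plan says.** The Statistical analysis section fixes the strata: "patients will be stratified as clinical responders versus non-responders at months 4, 12, and 24, based on the presence/absence of ASDAS low disease activity" (at or below 2.1), and "DAPSA low disease activity (≤14) for patients with PsA". Disease activity at the visit is the only criterion. The primary population is intention-to-treat and contains every included patient. A per-protocol analysis is added for robustness, but the article does not define it.

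The Assessments section applies the same cut-offs at the major visits (months 4, 12 and 24). Patients at or below them stay on ixekizumab. Those above them "change treatment at the discretion of the treating rheumatologist", and "they continue to be followed in the study".

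The Sample size calculation section plans sub-group analyses of the primary endpoint, including clinical responders against non-responders. It says the sample should be enough to detect a month-12 change in the whole population and "in the individual sub-groups during treatment with ixekizumab".

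**The concern.** One threshold does two jobs. At month 4 it decides who changes treatment; at months 12 and 24 it decides who is a responder, whatever drug was taken in between. A patient above the threshold on ixekizumab at month 4 and below it on another drug at month 12 moves from non-responder to responder. No rule in the article puts that patient elsewhere.

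The month-12 responder stratum can therefore hold two kinds of patient: those in low disease activity on ixekizumab, and those who did not respond to it and improved on something else. In the second kind, both the clinical state and the month-12 MRI reflect the later drug. In a single-arm study no comparator separates the two effects, so the responder versus non-responder contrast in WB-MRI change cannot be read as describing patients on ixekizumab.

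**Working it through.** **Following the rules for one patient**

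| Visit | Disease activity | Treatment rule (Assessments) | Stratum (Statistical analysis) |
|---|---|---|---|
| Month 4 | above threshold, on ixekizumab | change treatment, stay in follow-up | non-responder |
| Month 12 | at or below threshold, on another drug | none that affects the label | responder |
| Month 24 | at or below threshold, on another drug | none that affects the label | responder |

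A patient who first exceeds the threshold at month 12 and then changes drug can enter the month-24 responder stratum in the same way. Month-4 status is clean, because protocol-directed change begins only at that visit.

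**The plan's own figure.** The article gives no number for this point. The sub-group sentence rests on the sample size calculation: standardised change 24.8/26.2 = 0.947, two-sided 5% level, 80% power. An exact paired t-test needs 11 pairs (power 0.807), and the stated 12 pairs give 0.847. The figure reproduces closely, and nothing below depends on it.

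**Size at month 12 (assumed rates).** The document gives neither a switching rate nor a success rate on the later drug. Let s be the share switching at month 4 and q the share of switchers in low disease activity at month 12.

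Affected patients = N × s × q

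- N = 65, s = q = 0.30: 65 × 0.09 = 5.9
- N = 65, s = q = 0.50: 65 × 0.25 = 16.3
- N = 65 × 0.80 = 52 (the plan's 20% drop-out at month 12), s = q = 0.30: 52 × 0.09 = 4.7
- N = 52, s = q = 0.50: 52 × 0.25 = 13.0

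**Share of the responder stratum (a second set of assumptions, no drop-out).** Let p be the share in low disease activity at month 4. Suppose 80% of them still are at month 12, and all others switch.

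On-drug responders = 65 × p × 0.8; switched responders = 65 × (1 − p) × q

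- p = 0.6, q = 0.2: 31.2 and 5.2, so 5.2/36.4 = 14%
- p = 0.5, q = 0.3: 26.0 and 9.75, so 9.75/35.75 = 27%
- p = 0.4, q = 0.5: 20.8 and 19.5, so 19.5/40.3 = 48%

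No month-24 figure is offered, since it would need a further assumed round of switching.

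**The case against.** The article says clinical responders, not ixekizumab responders. A stratum defined by current disease state is legitimate, for instance when relating clinical status to MRI at the same visit. That stands: the grouping misleads only when read as response to the drug. But the article invites that reading. Its sample size sentence speaks of treatment with ixekizumab, and its endpoints concern patients treated with it. The sentence covers the whole population as well as the sub-groups, so the tension is wider than this rule; the responder strata are where it affects who is put in which group.

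It can also be said that the per-protocol analysis or the promised SAP will deal with switchers. The per-protocol set is undefined, so its effect is unknown, and it is only a robustness check. The article already fixes criterion, thresholds and visits, and a SAP that follows them inherits the mixture.

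How many patients leave ixekizumab is itself unsettled. The Study interventions section has ixekizumab given every 4 weeks to the end of the study and prohibits other potentially disease-modifying drugs except csDMARDs. The Assessments section has non-responders change treatment and stay in. These passages must be reconciled.

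Three stronger readings are tempting but unsupported:

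- **Response rates are inflated.** Table 3 lists no response rate as an endpoint.
- **The predictor regressions use a wrong outcome, or predictors would be reversed.** The article names neither outcome nor time point for them. They are affected only if they use month-12 or month-24 responder status, and nothing shows a reversal.
- **The primary result is misclassified.** Overall change in total inflammatory burden does not use the strata.

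**Conclusion.** The point holds for the month-12 and month-24 responder strata and the WB-MRI comparisons built on them. Followed as written, the rules mix on-drug responders with patients who improved after a change of treatment.

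The logic follows from the text, but the size does not. Under the assumed 30-50% rates, about 6-16 of 65 patients, or 5-13 of 52 after drop-out, would be affected at month 12. Under the second set of assumptions, switched patients make up 14-48% of the responder stratum. Both ranges are illustrations. The matter should be corrected before analysis, but it does not threaten the primary endpoint.

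**What to change.** - For months 12 and 24, define ixekizumab response as low disease activity while still on ixekizumab.
- Do not count patients who stopped ixekizumab as responders. Show them as a separate switched stratum in the MRI comparisons, so that their post-switch MRI stays out of the on-drug contrast. Simply moving them into the non-responder stratum would blur that contrast from the other side. In any response proportion, count them as non-responders.
- Report low disease activity regardless of drug under its own label.
- Add the responder comparison by month-4 status, which precedes protocol-directed switching, as a supporting analysis.
- Reconcile the Study interventions and Assessments sections on treatment after non-response.

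The cost of the redefinition is one sentence in the protocol or SAP and fewer patients counted as responders. It needs the date of each treatment change to be recorded, and it alters no treatment rule.

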### Endpoints

#### Primary endpoint

The primary endpoint is the change from baseline to month 12 in the total inflammatory burden in the entire body (peripheral and axial joints and entheses), as assessed by WB-MRI, in patients with axSpA and PsA treated with ixekizumab.

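### WB-MRI remission is taken from the same sum score as the primary outcome, so significance tests on change within and between remission strata cannot be interpreted

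*Protocol article*

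**What the plan says.** All statements are in the protocol article.

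- Primary endpoint: "The primary endpoint is the change from baseline to month 12 in the total inflammatory burden in the entire body", assessed by WB-MRI.
- Statistical analysis: "The total inflammatory burden in the entire body and the WB-MRI remission status will be determined using the sum score of WB-MRI scoring methods". The components are WIPE for peripheral inflammation, and CANDEN spine and SPARCC SIJ for axial inflammation.
- Sample size calculation: "Sub-group analyses in regard to the primary endpoints for all groups (axSpA vs. PsA, WB-MRI remission vs. WB-MRI non-remission", and clinical responders versus non-responders) are planned. The section adds that the sample size is adequate to show a significant change at month 12 in the individual sub-groups as well as overall.
- Statistical analysis: "patients will be stratified based on their diagnosis and WB-MRI remission status (remission versus non-remission"). No time point or cut-off is attached to remission. Clinical response does have time points: "patients will be stratified as clinical responders versus non-responders at months 4, 12, and 24".
- Statistical analysis: change within each sub-group gets a paired t-test or Wilcoxon signed rank test. Between sub-groups, "Comparisons between the sub-groups will be analyzed with an unpaired T-test (in case of normal distribution) or Mann-Whitney U test" is planned. The same strata are also applied to the WIPE and the CANDEN/SPARCC components separately.

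**The concern.** The stratifier and the outcome come from one score. The outcome is baseline score minus month-12 score. If remission means a low score at follow-up, membership of a stratum is decided by one of the two terms of the outcome. A test of change within such a stratum does not start from a valid null, and a test between the strata does not measure differential response to ixekizumab.

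This matters more than usual because the trial has a single arm and its main evidence is within-group change. Sub-group p-values on the primary endpoint would be printed next to the overall result and read as support for it, or as evidence that one kind of patient benefits more.

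**Working it through.** **The plan's own figure.** 3.6 × √53 = 26.2, and 24.8/26.2 = 0.947. An exact paired t-test calculation gives power 0.807 with 11 pairs and 0.847 with 12, so the stated 12 pairs is sufficient. It concerns the whole population and does not depend on the strata.

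**Inputs from the article.** Mean change 24.8, SD of change 26.2, 65 patients, 20% drop-out: 65 × 0.8 = 52 with month-12 data.

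**Assumed, because the article does not give them.** The SDs at baseline (sB) and month 12 (sF), their correlation r, the remission cut-off, and remission being judged at month 12.

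**1. Why the two are coupled.** Let B be the baseline score and F the month-12 score. Then cov(B − F, F) = r·sB·sF − sF². This is zero only when r·sB = sF. Otherwise change is related to remission even if the expected change is identical for everyone. Remitters show the larger reduction when r·sB < sF and the smaller one when r·sB > sF.

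**2. Between strata.** Call the lowest 35% of month-12 scores remission. For normal scores, the expected reduction in remitters minus that in non-remitters is (sF − r·sB) × k, with k = 0.3704/(0.35 × 0.65) = 1.628. Holding the SD of change at 26.2 and writing c = sF/sB gives sB = 26.2/√(1 + c² − 2rc).

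- c = 1, r = 0.4: sB = 23.92; 23.92 × 0.6 × 1.628 = +23.4
- c = 1, r = 0.8: sB = 41.43; 41.43 × 0.2 × 1.628 = +13.5
- c = 0.5, r = 0.4: sB = 28.42; 28.42 × 0.1 × 1.628 = +4.6
- c = 0.5, r = 0.8: sB = 39.06; 39.06 × (−0.3) × 1.628 = −19.1

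Simulation (n = 52, 4000 trials per setting) agrees. Differences in points:

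| Month-12 SD as share of baseline SD | r = 0.4 | 0.5 | 0.6 | 0.7 | 0.8 |
|---|---|---|---|---|---|
| 100% | 23.0 | 21.2 | 18.9 | 16.3 | 13.2 |
| 75% | 14.9 | 11.4 | 7.7 | 2.9 | −3.6 |
| 50% | 4.5 | 0.0 | −5.1 | −11.2 | −18.7 |

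Across r = 0.4 to 0.8, the unpaired t-test is significant in favour of remitters in 90% falling to 42% of trials with equal SDs, 51% falling to 1% at 75%, and 9% falling to 0% at 50%. At 50% it is significant against remitters in up to 73%.

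Skewed (gamma) scores show the same pattern. With baseline mean 40 (SD 30), month-12 mean 15.2 (SD 15) and cut-off 5, the mean reduction in remitters versus non-remitters is 37.7 versus 19.8 at correlation 0, but 11.2 versus 30.0 at 0.9.

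**3. Within the remission stratum, no true change.** Gamma scores with mean 40 and SD 30 at both visits, cut-off 15, n = 52, about 10 remitters per trial. The mean apparent reduction is 19.8, 13.2 and 7.4 points at correlation 0.3, 0.5 and 0.7. The paired t-test shows a significant reduction in 77%, 61% and 41% of trials, against a nominal 2.5% in that direction. Repeat runs move these by up to about 3 points (74% and 42% at the two ends). The SD of change in these runs is 36.1, 30.7 and 24.0, so they illustrate the mechanism and are not calibrated to 26.2.

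**The case against.** **Time point not stated.** The article does not say when remission is judged, and the cut-off and time point may properly be left to the SAP, which is to be written before any analysis. This stands: follow-up remission is an inference. It is a reasonable one, because participants must have moderate to high disease activity at entry, so a baseline remission stratum should be small. Baseline status would not remove the problem, since it is also coupled to change, through regression to the mean. The shared score, the sub-groups and the tests are already fixed in the article.

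**A positive result by construction.** A reader might infer that remitters will always appear to do better. The documents do not support this. That result needs the month-12 SD to be close to the baseline SD. For a lesion score expected to fall by 24.8 points, a smaller month-12 SD is plausible, and the contrast can then be null or favour non-remitters.

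**Clinical responders.** A reader might extend the circularity to these strata. As the article describes them, ASDAS and DAPSA contain no MRI score, so the same objection does not apply. Describing how clinical and imaging findings relate is also a listed secondary endpoint.

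**Limited reach.** The primary analysis uses all included patients, and remission strata appear in no listed endpoint. This stands and limits the severity. The article also mentions descriptive statistics, but it plans tests on these strata as well and says the sample size suits detection of significant change in each sub-group.

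**Conclusion.** The point holds as a matter of interpretation and should be fixed. Tests of change in total burden, or in its WIPE, CANDEN and SPARCC components, within or between WB-MRI remission strata are coupled to the stratifier. A significant within-remission reduction can arise with no true change in about 40% to 75% of trials at correlations 0.7 to 0.3. The between-stratum contrast can lie anywhere from about +23 to −19 points with no difference in expected response. Neither says anything about the drug effect in a sub-group or about differential effect.

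These sizes rest on assumed distributions, correlations and cut-offs, and on remission being a follow-up status. The coupling itself follows from the shared score. The primary result and the sample size are not in question.

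**What to change.** - Remove WB-MRI remission from the sub-groups tested on change in total burden and its WIPE/CANDEN/SPARCC components, or label those results descriptive and give no p-values.
- In the Sample size calculation section, withdraw the statement about detecting a significant change in individual sub-groups as far as it covers the remission strata.
- Report the proportion of patients in WB-MRI remission with a 95% CI as an outcome.
- Use remission as a stratifier only for outcomes outside the score: structural damage on CT or synthetic CT, clinical measures and patient-reported measures.

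The cost is wording in the protocol and the forthcoming SAP, with no change to data collection. The p-values for change in the remission strata are lost.
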